### Statistical Analysis

Data checking and cleaning will take place before analysis. Descriptive statistics for patient characteristics such as age, sex, caries prevalence, and the proportion of children with enamel defects will be reported. The total number of tooth sites included in the analysis will be reported.

Descriptive characteristics for the rater population will be reported, including qualification, clinical background, years of experience, and training results for each rater. Interrater and intrarater reliability for on-screen assessment of 3D models based on color and fluorescence using the intraclass correlation coefficient will be reported for all examiners. These estimates will be obtained from a multilevel model fitted to the surface-level data, accounting clustering (see below), and zero inflation.

To assess agreement among methods, we will undertake both surface-level and individual-level analyses. At the surface level, caries data naturally have 3 levels with surfaces clustered within a tooth, which are clustered within an individual. Therefore, for this analysis, we will use multilevel logistic regression to estimate method agreement while accounting for clustering for the tooth. Specifically, separate multilevel models will be fitted to compare VE with each of the alternative methods by including the variable method (VE vs on-screen assessment of 3D models in approximate natural colors, on-screen assessment of 3D models in approximate natural colors featuring fluorescence, and automated system) as the fixed effect. The coefficient estimates for the variable method will be used to indicate the level of agreement. The multilevel model will be fitted with a zero-inflated binomial distribution.

At the individual level, a numerical variable representing the number of lesions per individual will be generated and analyzed with 2 approaches. First, Bland-Altman method agreement analysis will be performed using a regression approach. Specifically, a model will be constructed to regress the difference between each pair of methods on their average [36]. The analysis will be repeated for each possible pair of methods. Second, for each possible pair of methods, an intraclass correlation coefficient will be estimated from a multilevel model fitted to the paired data consisting of the 2 measures for each individual obtained from the 2 methods, fitted with a zero-inflated Poisson distribution.

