## Discussion

This protocol aims to fill a knowledge gap by describing an approach for determining the diagnostic agreement between VE using ICDAS and on-screen assessment of 3D models featuring fluorescence obtained with an IOS.

Intraoral scanning is increasingly being adopted in dentistry as it offers improved clinical workflows for patient assessment and treatment planning, particularly in the disciplines of prosthodontics, orthodontics, and periodontics [13,38,39]. The role of scanning technology in supporting clinical diagnostics is an emerging research area [19,20,40-43]. There is paucity in the literature describing on-screen assessment of 3D models as a method for caries detection.

A strength of our study is the consideration of different approaches to analyze agreement. Our use of multilevel generalized linear regression models to analyze surface-level dental caries data has several strengths. First, caries from the same individual are more correlated than those between individuals. If this clustering is ignored, the estimated variance may be misleadingly small [44]. We will use multilevel models that account for clustering. Second, the multilevel regression approach allows for estimating method agreement while accounting for variability due to the influence of the rater and timing of assessment [45]. Finally, because all eligible primary teeth surfaces will be analyzed the high proportion of sound surfaces will result in zero-inflated outcome data. We will address this by fitting a generalized linear regression framework allowing the use of a zero-inflated binomial distribution; whereas traditional agreement methods, such as the κ statistic, are limited in this context [46]. A limitation of the statistical approach is that the coefficient estimates derived from the multilevel model do not quantify absolute agreement. As an alternative analysis, we will analyze the total caries at the individual level with a regression-based Bland-Altman agreement analysis [36]. The excess of zeros and, hence, the nonnormal distribution of the data precludes the calculation of the limit of agreement estimates that are clinically interpretable. Consequently, we will use the intraclass correlation coefficient derived from a multilevel model fitted with a zero-inflated Poisson distribution, acknowledging that this is influenced by the variability in the population.

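### The child-level zero-inflated Poisson ICC, as usually computed, barely responds when one method counts twice or half as many lesions, so it should not be read as evidence of interchangeability

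*Protocol article*

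**What the plan says.** The Statistical Analysis section plans two analyses at the level of the child: "a numerical variable representing the number of lesions per individual will be generated and analyzed with 2 approaches". The first is a Bland-Altman regression of the difference between two methods on their average. The second, repeated for every pair, is that "an intraclass correlation coefficient will be estimated from a multilevel model fitted to the paired data consisting of the 2 measures for each individual". The distribution named for this model is zero-inflated Poisson. No formula for the ICC is given, and no method term or between-method variance component is named.

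The Discussion gives the reasoning. At the surface level, "the coefficient estimates derived from the multilevel model do not quantify absolute agreement". At the child level, the excess of zeros "precludes the calculation of the limit of agreement estimates that are clinically interpretable". The ICC is brought in for that reason: "Consequently, we will use the intraclass correlation coefficient derived from a multilevel model fitted with a zero-inflated Poisson distribution". Dependence on population variability is the only caveat attached to this ICC ("acknowledging that this is influenced by the variability in the population"). The Discussion closes by saying that the results will inform whether 3D models and visual examination (VE) can be used interchangeably.

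**The concern.** In a Poisson random-intercept model the within-child variance is set by the mean. No residual is estimated from how far the two methods differ. A constant ratio between methods goes into the mean, or into a method coefficient if there is one, and the usual ICC counts neither as disagreement. What remains is mainly the spread between children.

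Systematic over- or under-counting is a main way in which two methods fail to be interchangeable, and some shift is foreseeable here. The VE protocol could not score ICDAS code 01 on smooth surfaces, whereas the on-screen index merges codes 01 and 02 as initial caries, which is also the main detection threshold. The ICC is brought in because the other analyses are said not to give an absolute or clinically interpretable measure. If it too ignores a shift, a value above 0.9 could be quoted as agreement when one method finds twice as many lesions.

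**Working it through.** **Inputs.** From the Protocol article: two counts per child, a zero-inflated Poisson multilevel model, and 213 children (Results). The article gives no lesion counts and no ICC, so there is no figure to reproduce. Assumed: mean lesions among children with caries, between-child variance s² on the log scale, proportion caries-free, and a method ratio of 1, 2 or 0.5.

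**Formulas.**
- Usual log-scale ICC = s² / (s² + ln(1 + 1/M)), with M the mean count.
- With between-method variance: s² / (s² + d²/2 + ln(1 + 1/M)), with d the log ratio. For a twofold shift d²/2 = (ln 2)²/2 = 0.24.
- Concordance (absolute agreement) = 2·cov / (var_A + var_B + (mean_A − mean_B)²).

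**One case by hand** (s² = 1, no caries-free children).
- Equal means of 5: ln(1.2) = 0.182, so the ICC is 1/1.182 = 0.846. The log-normal spread gives a covariance of 25(e − 1) = 42.96, so concordance is 42.96/(42.96 + 5) = 0.896.
- Twofold shift, means 5/√2 = 3.54 and 5√2 = 7.07, average 5.30: ln(1 + 1/5.30) = 0.173, so the ICC is 1/1.173 = 0.853. The variances are 3.54 + 12.5(e − 1) = 25.01 and 7.07 + 50(e − 1) = 92.98, and the squared mean difference is 12.5. Concordance is 85.91/130.50 = 0.658.
- With between-method variance the ICC is 1/(1 + 0.24 + 0.173) = 0.708.

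The usual ICC rises slightly while concordance drops by 0.24.

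**Exact doubling in every child.** With variance v and mean m for the lower-counting method, concordance is 4v/(5v + m²), always below 0.80. For v/m² of 0.5, 1, 2, 4 and 10 it is 0.57, 0.67, 0.73, 0.76 and 0.78.

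**Fitted models.** Zero-inflated Poisson random-intercept models were fitted by maximum likelihood to simulated pairs, 213 children, 30 replicates. Each cell shows equal counts → twofold difference.

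| Mean, s², caries-free | Log-scale ICC | Count-scale ICC | Log-scale ICC with method variance | Concordance |
|---|---|---|---|---|
| 5, 1, 40% | 0.91 → 0.92 | 0.98 → 0.97 | 0.92 → 0.87 | 0.91 → 0.69 |
| 15, 0.5, 10% | 0.94 → 0.92 | 0.95 → 0.84 | 0.94 → 0.73 | 0.92 → 0.62 |
| 10, 0.3, 0% | 0.75 → 0.75 | 0.77 → 0.76 | 0.75 → 0.47 | 0.76 → 0.44 |
| 2, 0.5, 40% | 0.78 → 0.81 | 0.88 → 0.87 | 0.78 → 0.75 | 0.65 → 0.55 |
| 5, 1, 40%, same lesions | 0.93 → 0.90 | 0.99 → 0.97 | 0.92 → 0.84 | 0.99 → 0.73 |
| 2, 0.5, 40%, same lesions | 0.86 → 0.77 | 0.96 → 0.90 | 0.86 → 0.71 | 0.96 → 0.67 |
| 10, 0.3, 0%, same lesions | 0.78 → 0.72 | 0.80 → 0.74 | 0.78 → 0.49 | 0.98 → 0.53 |

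In the first four rows the two counts are independent Poisson draws given the child, and one method's expected count is twice the other's. In the last three both methods score the same true lesions, first at equal detection rates and then with one detecting half as many. The two log-scale columns and the count-scale column come from models without a method term, except that the method-variance column needs one. Adding a fixed method term changed the usual log-scale ICC by about 0.01.

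**Many caries-free children.** With 30 to 50% structural zeros and gamma-Poisson counts of mean 3 to 6 in the rest, the log-scale ICC was 0.93 to 0.95 for identical counts, 0.95 to 0.97 for doubled and 0.90 to 0.94 for halved. The absolute-agreement ICC was 1.00, 0.71 to 0.75 and 0.70 to 0.74. Other draws and parameter choices of this kind took the log-scale ICC down to 0.88.

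The last table row shows the reverse problem: almost identical counts (concordance 0.98) give an ICC of only 0.78, because the children differ little.

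**The case against.** **Other analyses would show the shift.** A reader might infer that the plan conceals a systematic over- or under-count. The documents do not support that. The Bland-Altman regression is planned for every pair, and the Discussion gives up only the limits of agreement. Under exact doubling the difference is x and the average 1.5x, so the slope is 1/1.5 = 0.67. In simulations of the scenarios with many caries-free children (500 replicates) the mean slope was 0.67 for doubling and −0.61 to −0.64 for halving, significant in every replicate. The surface-level method coefficient also targets such a shift. This stands, and it limits the point to how the ICC is read.

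**The model is not at fault in itself.** A reader might also infer that any ICC from this model misleads. It does not follow. The article gives no formula, a fuller plan may define one, and the same model with between-method variance in the denominator does respond. What remains is that the article fixes the model, distribution and paired data, names no such component, and mentions population variability as the only weakness. Even the amended log-scale ICC can fall modestly where children differ widely (0.92 to 0.87, against 0.91 to 0.69 for concordance).

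**Near-perfect against poor is too strong a contrast.** ICCs of 0.90 or more need wide between-child spread or many shared caries-free children. The Discussion's expected excess of zeros makes this plausible but does not establish it. Otherwise the ICC is nearer 0.75 to 0.83, with or without bias. Concordance of 0.70 to 0.75 is not plainly poor.

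**The scenarios are large and assumed.** Only twofold shifts were tested. The automated system scores primary molar occlusal surfaces only, at most eight per child, so exact doubling is impossible for some children in that comparison.

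**Conclusion.** The point holds as a should-fix. The ICC that the text describes, computed in the usual way on the log scale, is mainly a measure of between-child spread. Under a twofold systematic difference it moved by at most 0.09 in the 30-replicate runs, usually by 0.00 to 0.05 and sometimes upward, while concordance fell by 0.10 to 0.45. With many caries-free children it stayed mostly at about 0.88 to 0.97 while concordance fell to about 0.70 to 0.75; at low counts (mean 2) it was lower, 0.77 to 0.86, and still moved much less than concordance when both methods scored the same lesions. The count-scale version is less blind in some settings (0.95 to 0.84).

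The sizes rest on assumed counts, twofold shifts and the usual ICC definition. That the usual definition contains no between-method term does not depend on those counts. The consequence is confined to this coefficient: a high value would not by itself support interchangeability.

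**What to change.** For each pair of methods, report an absolute-agreement index on the child lesion counts: Lin's concordance coefficient, or a two-way absolute-agreement ICC with between-method variance in the denominator. Take its confidence interval from a bootstrap that resamples children, which needs no normality assumption. Beside it, report the mean difference or the ratio of counts per child with a 95% CI.

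The zero-inflated Poisson model may be kept on one of two conditions: its ICC is stated to include between-method variance, or it is described only as a measure of variation between children. Add to the Discussion's caveat that, without that component, the ICC does not reflect systematic differences between methods.

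The cost is a change of wording and a few lines of analysis, with no new data. The reported agreement may look less favourable.

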## Methods

### Aims and Objectives

The specific study objectives are to, first, determine and compare the diagnostic agreement between VE and on-screen visual assessment of 3D models in approximate natural colors with and without fluorescence to detect and classify carious lesions on visible tooth surfaces in primary teeth. The second objective is to determine the diagnostic agreement between VE and the automated caries scoring system for detecting and classifying occlusal carious lesions in primary teeth. Finally, the third objective is to explore the impact of caries threshold, tooth surface examined (smooth vs occlusal), and enamel defects’ presence on the reported agreement estimates between caries detection methods.

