### Study Design

This is a diagnostic agreement study, as VE is not considered a gold standard in this setting [23]. Dental caries in this study is defined as primary coronal caries. Data sources (age at dental visit, sex, VE data, and 3D models) will be retrospectively sourced from a sample of children who underwent VE using the ICDAS and intraoral scanning with the TRIOS 4 to produce 3D digital models.

The 3D models for each eligible participant will be subject to an on-screen assessment by 4 qualified dental practitioners. Each practitioner will examine all 3D models at 2 separate time points. An on-screen assessment of 3D models based on tissue geometry and approximate natural colors (excitation to visible white light) will take place first (Figure 1A), followed by an on-screen assessment with the addition of fluorescence texture (excitation to light at 415 nm; Figure 1B). An interval of at least 4 weeks will follow to minimize recall bias before the on-screen assessment process is replicated. Occlusal surfaces of primary molars will be examined using the automated caries scoring system at a single time point only (Figure 1C). Examiners will be blinded to all clinical examination data and automated caries scores when scoring the 3D scans.

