### Tooth Surface Inclusion Criteria

For each participant, a tooth surface will be eligible for on-screen assessment if it (1) has been examined as part of the dental exam, (2) is from a primary tooth, and (3) is visible on the 3D model.

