#### Intraoral Scanning

Immediately following the VE, intraoral scanning took place using the TRIOS 4 scanner. This generation scanner has a high accuracy and fast acquisition time relative to other scanners on the market for complete arch scanning [32]. It also has specialized fluorescence technology built into its hardware which exposes teeth to 415-nm light during scanning. Light emitted from the teeth passes through a filter in the scanner (which filters out blue light) to be received by the scanner sensor. The fluorescence signal overlays onto the 3D models as green fluorescence and red fluorescence texture, aided by commercial software (TPM; version 2.3, Dental Desktop and TRIOS; 3Shape TRIOS A/S).

The clinical examiners were trained to use the 3Shape TRIOS software interface and intraoral scanning protocols. Before scanning, the dental lamp was switched off, and the window blinds were closed to limit external light during the scanning process as per manufacturer instructions [33]. Teeth were dried with gauze or cotton rolls, and the manufacturer-recommended scanning strategy was followed. The scanning procedure was considered adequate when the software had obtained sufficient information about tooth color and fluorescence for the region of interest. If the scan was incomplete, the reasons why the scanning procedure was inadequate were documented. The reasons for insufficient scan data included the scanner tip being too big to accommodate, gag reflex, and behavioral or developmental issues that limited cooperation with the scanning procedure. Both complete and incomplete 3D models were saved with the participant's unique identifier in the dental desktop software.

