A sensitivity analysis will explore the impact of the diagnostic threshold used on agreement estimates. Analyses will be repeated with the caries data dichotomized at alternative thresholds: the moderate and extensive thresholds. In the analysis of the moderate threshold, sound and initial surfaces will be labeled caries absent (0) and all remaining categories (moderate-extensive) will be labeled caries present (1). In the analysis of the extensive threshold, sound, initial, and moderate caries will be combined and labeled as caries absent (0) and only teeth with extensive caries will be marked as caries present (1). To evaluate if the surface location and presence of enamel defects impact the diagnostic agreement estimates, these variables will be included as additional variables in the regression models for the surface-level analyses, including interaction terms with the method. The surface location variable will have 3 levels for each visible tooth surface (occlusal, smooth, and proximal). Enamel defects will be a binary variable, defined as present or absent per person. The sensitivity analysis to compare the agreement between on-screen assessment of 3D models in approximate natural colors and on-screen assessment of 3D models in approximate natural colors featuring fluorescence will include additional variables, rater and timing, as fixed effects.

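### In the exploratory on-screen analyses for Objective 3, the method-by-surface-location interaction is partly confounded with tooth type, because occlusal surfaces lie only on molars and many smooth surfaces lie on anterior teeth

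*Protocol article*

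**What the plan says.** All references are to the protocol article.

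- **Aims and Objectives.** The third objective is exploratory. One of the factors whose impact on agreement is to be examined is "tooth surface examined (smooth vs occlusal".
- **Statistical Analysis, sensitivity analysis paragraph.** Two variables are named for this purpose, surface location and enamel defects: "these variables will be included as additional variables in the regression models for the surface-level analyses, including interaction terms with the method". On the first: "The surface location variable will have 3 levels for each visible tooth surface (occlusal, smooth, and proximal". The comparison of color with color plus fluorescence "will include additional variables, rater and timing, as fixed effects". Tooth type (molar versus incisor or canine) appears nowhere as a covariate, interaction, stratum or restriction.
- **Statistical Analysis, main surface-level model.** "we will use multilevel logistic regression to estimate method agreement while accounting for clustering for the tooth".
- **Tooth Surface Inclusion Criteria.** For on-screen assessment, eligibility depends on a surface having been examined and on two further conditions: "2) is from a primary tooth, and (3) is visible on the 3D model". Anterior teeth therefore enter.
- **Study Design.** The automated system is confined to molars: "Occlusal surfaces of primary molars will be examined using the automated caries scoring system at a single time point only".

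**The concern.** An interaction between method and surface location is meant to show whether agreement differs by the kind of surface. The two groups compared also differ in the kind of tooth. The occlusal group is made up entirely of molar surfaces, and the smooth group mixes molar and anterior surfaces. Suppose the two methods diverge more on one tooth type than on the other, for whatever reason. The model then has no term to carry that difference except the method-by-location interaction.

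Clustering by tooth does not remove it. A tooth-level random intercept absorbs how carious a tooth is under both methods. It does not absorb a method effect that itself varies by tooth type.

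At stake is the interpretation of one exploratory result. The study could attribute to surface type what belongs to tooth type, or miss a real surface effect because a tooth-type effect offsets it.

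**Working it through.** The article gives no surface counts by tooth type, no prevalence by tooth type and no method effect by tooth type, so it has no figure of its own to reproduce. All numerical inputs below are assumptions.

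**1. Composition of the smooth group.** Assume 20 primary teeth (8 incisors, 4 canines, 8 molars) and two smooth surfaces (buccal and lingual) per tooth. With L incisors shed, the anterior share of smooth surfaces is 2(12 − L) / [2(12 − L) + 16].

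| Incisors shed | Anterior smooth | Molar smooth | Anterior share |
|---|---|---|---|
| 0 | 24 | 16 | 24/40 = 60.0% |
| 2 | 20 | 16 | 20/36 = 55.6% |
| 4 | 16 | 16 | 16/32 = 50.0% |
| 6 | 12 | 16 | 12/28 = 42.9% |
| 8 | 8 | 16 | 8/24 = 33.3% |

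The occlusal group is 8 of 8 on molars. The target age is 4 to 6 years (Participant Eligibility Criteria), so some children will have shed incisors. Surface exclusions will shift the shares further.

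**2. Illustrative size, marginal calculation.** Assume no surface effect, VE prevalence of 8% on every surface, a method log odds ratio (OR) of 0 on molars and b on anterior teeth, and a full dentition.

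- VE odds = 0.08/0.92 = 0.0870.
- On-screen prevalence on anterior teeth: q = 0.0870·e^b / (1 + 0.0870·e^b).
- On-screen prevalence on all smooth surfaces: 0.6q + 0.4 × 0.08.
- The occlusal OR is 1, so the smooth-versus-occlusal ratio of ORs is the pooled smooth OR.

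| b | q | Pooled smooth prevalence | Ratio of ORs | Log |
|---|---|---|---|---|
| 0.4 | 0.1148 | 0.1009 | 1.29 | 0.26 |
| 0.7 | 0.1490 | 0.1214 | 1.59 | 0.46 |
| 1.0 | 0.1912 | 0.1467 | 1.98 | 0.68 |

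About two thirds of the assumed anterior-molar difference (0.26/0.4 = 65%; 0.68/1.0 = 68%) appears as a surface effect. With 8 incisors shed (share 1/3), the same formula gives pooled prevalences of 0.0916 and 0.1171 for b = 0.4 and 1.0, and ratios of 1.16 and 1.52.

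Sensitivity to prevalence, full dentition, b = 0.4 to 1.0:

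- anterior 4%, molar 8%: log ratios 0.19 to 0.55, that is 1.2 to 1.7;
- anterior 10%, molar 8%: the upper end is 0.71, that is about 2.0;
- anterior 10%, molar 5%: 0.30 to 0.78, that is 1.35 to 2.2. A value of 2.2 is reached only by also lowering molar prevalence.

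**3. Does clustering by tooth cure it?** A simulation of 20,000 children used random effects for person, tooth and surface, no true surface difference in the method effect, and a method OR of 1 on molars. The interaction was estimated from within-surface discordant pairs, which removes every person, tooth and surface intercept.

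| Anterior method OR | Ratio of ORs, all teeth | Ratio of ORs, molars only |
|---|---|---|
| 2 (three anterior prevalence settings) | 1.42 to 1.59 | 0.97 to 1.01 |
| 3 | 2.05 | 1.00 |

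The bias remains after all intercepts are removed, and it disappears in the within-molar contrast (true value 1.00).

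**The case against.** **The estimand may be descriptive.** Objective 3 is exploratory, and the analysis sits in the sensitivity analysis paragraph. Read as agreement on occlusal and smooth surfaces as they occur in children's mouths, the all-teeth contrast is valid. This stands, and it is why that contrast should be kept. It does not cover a statement that the surface examined has an impact on agreement, which is how the objective is worded.

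**A full analysis plan may add the term.** That is possible. However, the article presents itself at the end of its Introduction as describing the statistical analysis plan, and it names the covariates. What it names leaves the two factors mixed.

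**The mechanism and the size are assumed.** This stands in full. A reader might infer from "The reasons for insufficient scan data included the scanner tip being too big to accommodate, gag reflex" that scans perform worse on posterior teeth. The text gives these as reasons for insufficient data, and surfaces with less than one-third visible for that reason are excluded. The documented consequence is mainly missing surfaces, not different caries calls on the surfaces analysed. VE without magnification applied to every tooth and shows no difference by tooth type.

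**60% is not assured.** It holds only for a full dentition, so the smooth group need not be mostly anterior. The argument needs only a substantial anterior share.

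**Two levels against three.** A reader might see an error in the objective naming two surface levels while the analysis uses three. It is not one: the three-level variable contains the smooth-versus-occlusal contrast.

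**Conclusion.** The point holds as a partial confounding of one exploratory interaction. Occlusal surfaces are all on molars, a substantial share of smooth surfaces are not, and the named covariates include nothing that separates surface type from tooth type. The random effect for tooth does not do so either.

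How much this matters depends on whether the scan-versus-VE difference varies between molars and anterior teeth, and the document is silent on that. The ratio of 1.3 to 2.0 is conditional on an assumed anterior log OR of 0.4 to 1.0 against 0 on molars, equal 8% prevalence and a full dentition. It is smaller if incisors have been shed. It comes from a marginal calculation, not from the zero-inflated multilevel model in the plan.

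A reader might go further and infer that the surface result will be false, or that the study's main agreement estimates are biased. The document supports neither. Objective 2 uses molar occlusal surfaces only, so location does not vary there. The main Objective 1 estimates and the individual-level analyses do not use the interaction.

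**What to change.** In the sensitivity analysis paragraph of Statistical Analysis:

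1. Keep the planned all-teeth method-by-location contrast and label it descriptive.
2. For the on-screen comparisons, either add tooth type (molar or anterior) and its interaction with method to the same model, or report the occlusal-versus-smooth interaction within primary molars alongside the planned one.
3. State that any conclusion about the effect of surface type rests on the estimate from step 2.

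No new data are needed, because caries was recorded for each tooth surface. The cost is one covariate with its interaction, or one restricted analysis, and lower precision: the within-molar contrast uses 16 rather than 40 smooth surfaces per child in a full dentition.
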